### Alpha determination:

Miller et al. (2019) discuss a method for estimating the optimal alpha that accounts for base rate (<https://www.ncbi.nlm.nih.gov/pmc/articles/PMC6314595/>). Base rate of depression symptom improvement with mindfulness alone was estimated at 66-76% (<https://www.ncbi.nlm.nih.gov/pmc/articles/PMC2791668/#B5>), based on effect sizes from Khoury et al. (2015). Using this base rate and an anticipated sample size <50, alpha was set at a conventional 0.05. Due to the early phase nature of this trial, we will not correct the alpha level of secondary clinical outcomes for multiple comparisons.

### Exploratory Analysis

### Develop an algorithm with Storyline Health technology to rapidly discover the most predictive and information rich components in the assessment of burnout and its treatment response, utilizing the Storyline Integrative Assessment

1. The objective is to create an effective and fast algorithm for feature selection and question selection to build assessments, diagnostic biobehavioral markers and predictive models from Storyline captured speech, vocal and facial data. The proposed algorithm has 3 components, including (1) rapid feature and question filtering based on variance, (2) feature selection using a method that integrates mutual information and random forest importance scores and (3) question selection using a deep learning method that ranks the predictive value of each question using the optimized features. The steps are as follows:

*Rapid Question Filtering* – The first step in the Short Story algorithm will be to filter questions, assessments and A.I. features in the storyARC and storyTIME files that have little information content. To do this, we will compute the variance for each measured feature for each question in the data for all people in a customer’s pilot study. The variance is scaled to account for differences in units. We then sum the variance for each feature for each question, apply a min-max absolute scale for interpretation that scores questions from 0 (low information content) to 100 (high information content). The results will enable users to rapidly screen, rank and prune questions with little to no information content by pruning the bottom 25% of tested candidate questions.

*Feature Selection:* Storyline AI measures over 20,000 speech, vocal and facial features from the responses for each question and many are correlated or not useful for detecting some phenotypes of interest. Therefore, in this second step, Short Story technology performs a feature selection analysis that uncovers the most useful features for each tested question in an assessment for predicting a particular phenotype or outcome. The major objective is to uncover the best questions and features when the available data has limited sample size and classes are imbalanced. Our approach will involve implementing the qualitative mutual information (QMI) feature selection algorithm previously detailed by others and proven for high dimensional data, including microarray data for tens of thousands of genes (Nagpal and Singh, 2019). The algorithm will provide a score that combines random forest (RF) feature importance scores with mutual information to obtain a QMI value for each feature. QMI is more powerful than random forest (RF) importance or mutual information alone for feature selection, as previously described (Nagpal and Singh, 2018). In brief, RF will be applied to the speech, vocal and facial feature sets separately for each question and the importance scores of each feature will be calculated, as well as mutual information. RF importance scores will be converted to Preference scores and multiplied by the mutual information to define QMI values for each feature. The features will then be ranked by QMI values and features with a QMI > 0 will be retained. The results will return the most useful speech, facial and vocal features for each question. The usefulness of the features is determined from their ability to differentiate the two classes in a study, such as control versus sick patients.

This approach has many advantages, including broad utility with few parameters to tune, applications to diverse data types with few samples and acceptable computational speed. RF importance scores are powerful for ranking correlated features. Mutual information, which determines the amount of information one random variable can provide about another variable, is then incorporated to further help remove irrelevant and redundant features. When accounting for accuracy and computational efficiency, this combined approach outperforms most methods, including filter, wrapper, embedded and hybrid feature selection strategies (Nagpal and Singh, 2019).

*Question Selection:* The final step of the Short Story algorithm will provide a score that determines the individual questions that should be retained in a new assessment and those that can be eliminated. In this approach, the input is all of the candidate questions and their optimized speech, vocal and facial features revealed from Short Story Score #2. The individual questions and question combinations that show the most value for predicting the classes of interest will then be determined. We will create a simple two-layer neural network that is architected to take Storyline speech, vocal and facial features as inputs to predict the phenotypic classes of interest. The algorithm will be designed such that questions are tested in all possible pairwise combinations with 5-fold cross validation. The mean accuracy for predicting the target phenotype is determined for each question combination. Each pairwise question combination is then assigned an index. To compute the Short Story score for each question, we multiply the index and the mean classification accuracy for all question pairings in which that question was included in the predictive model. This vector of index*accuracy values is summed to yield a score and then the scores for all of the candidate questions are min-max scaled to create the final Short Story question ranking score from 0-to-100, where a high score indicates important questions, and a low score indicates questions that can be pruned. The final results will return the ranking for each question and the mean classification accuracy values for each question.

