## Exploratory Objectives

### To capture and explore behavioral data markers using the Storyline Health AI platform that may relate to other study outcomes and which may inform future research utilizing the Storyline Health Integrative Assessment tool.

We will be utilizing *Storyline Health* to track user questionnaires, experiences and other study data. This is a recently developed system that will allow us to track a variety of behavioral data points previously difficult to track including micro-expressions, pupillometry, voice tone, cadence and prosody, among other markers. Storyline Health is a platform that allows scalable, remote, and objective profiling of human cognition, expression, and behavior using a video-enabled smartphone. Storyline enables researchers to create clinical and behavioral assessments and care pathways, deploy them at scale to user smartphones and capture video responses that are securely stored in the cloud. The researcher then launches the Storyline AI pipeline, which extracts over 20,000 different measures of human facial, speech, and vocal patterns in each video, such as sub-second facial micro-expressions, facial blood flow patterns, word choice, sentiment, and vocal micro-tremors. The de-identified data is stored in storyARC and storyTIME files for download, analysis and sharing. Using Storyline, precise biomarkers and predictive models of illness, disease subtypes, drug responses and outcomes can be discovered, validated and then delivered instantly to providers and patients through **Storyline Telehealth**. The **Storyline Library** is an “App-like store” that makes proven assessments, models and care pathways available to providers. Therefore, Storyline seamlessly integrates clinical research with care delivery at scale, enabling rapid translation of biomarkers and algorithms.

*Tertiary Endpoint:*

- We will deploy the Storyline Integrative Assessment (see Appendix 1) to narrow in on specific feature selection in small cohorts of patients with deep AI phenotyping to identify behavioral phenotype predictors of burnout, which is heterogeneously characterized. This will be administered to both study arms at baseline, at the primary outcome point (2 weeks post intervention on both study arms), and at 6 months post intervention.

*Tertiary Endpoint:*

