This project will be employing Storyline Health technology. Storyline Health is an AI platform that enables deep AI phenotyping of facial, speech and vocal patterns captured from asynchronous clinical interviews delivered over a smartphone. These innovations include the creation of technology for asynchronous clinical interviewing with simultaneous video capture, software for creating and delivering novel assessments, a military-grade data security solution for safely storing patient video data, an AI pipeline that extracts over 20,000 different measures from patient facial, speech and vocal patterns and architects them into easy to use, de-identified storyARC and storyTIME data file types that we created to enable research, discovery and model development. Storyline Health involves innovative technologies to deliver proven assessments, biobehavioral markers, care pathways and predictive models into clinical care settings at massive scale through the Storyline Library (an app-like store for AI health models) and Storyline telehealth. The clinical category of ‘burnout’ is heterogeneous in characterization and poorly understood. This limits both prediction of features of burnout among clinicians as well as meaningful interventions to address symptoms of burnout. We will be using the Storyline Integrative Assessment to build a model for diagnosing and tracking symptoms of burnout as well as predicting treatment response, particularly given how heterogeneously characterized this condition is at present. Similarly, the field of psychedelic-assisted therapy is in early stages: there are limited studies at present to inform questions as to treatment response and prediction of adverse outcomes. Storyline Health offers a unique and powerful way of informing many of these foundational questions for the field.

We have an ongoing relationship with Usona, a pharmaceutical company that manufactures psilocybin and which is providing the psilocybin for our HOPE clinical trial. Our research group is committed to the Statement on Open Science and Open Praxis with Psilocybin, MDMA, and Similar Substances: https://files.csp.org/open.pdf

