## Number of Patients

This study will enroll a total of 24 patients with 12 patients in each study arm.

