# ELIGIBILITY CRITERIA

Potential study participants must meet all inclusion criteria and no exclusion criteria to be deemed eligible for trial participation. To ensure subject safety, all patients must be deemed eligible at the time of study registration and must continue to meet eligibility criteria up to the first group therapy session. This eligibility checklist is used to determine subject eligibility and will be filed with the enrolling investigator’s signature in the subject research chart.

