**Yes/No Eligibility Questions (Response of “no” = subject ineligible)**

- PHQ-9 score ≥ 10 and meet DSM-5 criteria for a depressive disorder, including adjustment disorder with depressed mood.
- Meet our working definition of burnout which will involve a score on the emotional exhaustion subscale (≥ 27) and a ‘high’ score on one other subscale (either depersonalization ≥ 13 or personal accomplishment ≤ 21).
- Not taking regularly scheduled medications to treat depression and/or anxiety, including benzodiazepines, for at least 4 weeks prior to administration of psilocybin, if randomized to that study arm.
- Fluent in English.
- Reading literacy and comprehension sufficient for understanding the consent form and study questionnaires, as evaluated by study staff obtaining consent.
- Able to provide informed consent and willing to sign an approved consent form that conforms to federal and institutional guidelines.
- ECOG Performance Status ≤ 2.
- Have a support person that would be able to escort the subject home on the evening of the psilocybin dosing session. The use of ride services will not be permitted (e.g., Uber, Lift, taxi, etc.)
- (If randomized to psilocybin arm) Adequate liver function as defined as:
  - Total Bilirubin < 1.5x institutional upper limit of normal (ULN) unless elevated bilirubin is related to Gilbert’s Syndrome.
  - AST(SGOT)/ALT(SGPT) <3 x institutional ULN
  - For female subjects: Negative pregnancy test and agreement to use highly effective contraception or evidence of post-menopausal status if randomized to psilocybin arm. The post-menopausal status will be defined as having been amenorrheic for 12 months without an alternative medical cause.
  - For male subjects: agree to condom use during intercourse for 24 hours post-psilocybin dose.
  - Agree to refrain from using any psychoactive drugs, including alcoholic beverages, ondansetron, cannabis, and non-routine PRN medications within 24 hours of the psilocybin administration. Exceptions include daily use of caffeine, nicotine, and opioid pain medication.
  - Agree that for one week preceding the psilocybin session, he/she will refrain from taking any nonprescription medication, nutritional supplement, or herbal supplement except when approved by the research team. Exceptions will be evaluated by the research team and will include acetaminophen, non-steroidal anti-inflammatory drugs, and common doses of vitamins and minerals.

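### All participants meet the burnout definition at entry, so the baseline Storyline recordings cannot yield a diagnostic marker of burnout, and with that label the two-class retention rule keeps no feature

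*Protocol*

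**What the plan says.** **Aim.** The first tertiary endpoint in Section 1.3 uses Storyline "to identify behavioral phenotype predictors of burnout, which is heterogeneously characterized". Section 2 says the tool will "build a model for diagnosing and tracking symptoms of burnout as well as predicting treatment response". The opening of the Exploratory Analysis in Section 12.2 repeats the diagnostic purpose: "to build assessments, diagnostic biobehavioral markers and predictive models from Storyline captured speech, vocal and facial data". Prediction of treatment response is a separate tertiary endpoint in Section 1.3.

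**Method.** Under Feature Selection in Section 12.2, a feature's usefulness is its power to tell two classes apart; controls against patients is the example given. QMI is a preference score, derived from random-forest importance, multiplied by mutual information. The retention rule is: "The features will then be ranked by QMI values and features with a QMI > 0 will be retained".

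**Population.** Section 5.1 requires each participant to "Meet our working definition of burnout which will involve a score on the emotional exhaustion subscale" of at least 27, together with depersonalization of at least 13 or personal accomplishment of at most 21. Section 5 adds that participants "must continue to meet eligibility criteria up to the first group therapy session". Section 4.2 gives the size: "This study will enroll a total of 24 patients with 12 patients in each study arm". The comparator arm is made up of participants with burnout who receive MBSR alone.

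**Timing.** Table 2 schedules both Storyline and the MBI at weeks 1, 11 and 33. The week 1 questionnaires come before the first MBSR session.

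**The concern.** A marker that diagnoses a condition has to separate people who have it from people who do not. This protocol fixes three things that do not fit together at baseline: a diagnostic aim, a two-class selection method, and an entry rule that admits only one of the two classes. Baseline is also the only Storyline assessment that treatment has not touched.

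Two consequences follow. Applied literally to burnout yes/no at baseline, the algorithm returns an empty feature set. If a second class is then sought by combining baseline with later recordings, the features selected may reflect visit, practice with the same video tasks, or treatment, and could be reported as features of burnout.

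**Working it through.** The protocol gives no sample size, power or error rate for this analysis, so there is no figure to reproduce. The check applies the stated rule to the stated population.

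**1. Baseline, label = burnout yes/no**
- Inputs: 24 participants (Section 4.2), all meeting the burnout definition (Sections 5 and 5.1). The Study Summary gives 25 subjects; the result is the same.
- Label entropy: H(Y) = −Σ p·log₂p with p = 24/24 = 1, so H(Y) = 0 bits.
- Mutual information satisfies I(X;Y) ≤ H(Y), so I(X;Y) = 0 for every feature X.
- QMI = preference score × 0 = 0. The condition QMI > 0 fails for every feature.
- The binary cut-points in the Secondary Analysis (emotional exhaustion ≥ 27, depersonalization ≥ 13, or personal accomplishment ≤ 21) do not help. Everyone already has emotional exhaustion ≥ 27, so everyone is positive.
- A numerical check with 20,000 features and 24 of 24 in one class kept 0 features.

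**2. Any label with a second class**
- If one of 24 participants remits by week 11, H(Y) = (23/24)·log₂(24/23) + (1/24)·log₂24 = 0.059 + 0.191 = 0.25 bits. The step 1 result no longer applies.
- Simulation with 20,000 pure-noise features, one run per split. Assumed settings, not in the protocol: 500 Gini trees, √p candidate features per node, plug-in mutual information on tertiles, QMI taken as importance × mutual information.

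| Assumed class split | Features with QMI > 0 |
|---|---|
| 24 / 0 (baseline) | 0 |
| 23 / 1 | 304 |
| 20 / 4 | 615 |
| 16 / 8 | 894 |
| 12 / 12 | 906 |
| 10 / 6 (16 completers) | 599 |

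So the empty result belongs to the baseline burnout label alone. With any second class the rule keeps hundreds of features, and in this simulation all of them are noise.

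**3. What the second class means**
- *Within week 11 or week 33:* both classes share the same visit and the same number of earlier recordings, and all have been assigned an active intervention. The contrast is remitters against non-remitters after treatment, which is a remission question and overlaps the response endpoint.
- *Baseline and week 11 pooled:* suppose r of 24 remit (assumed; no attrition). All r records without burnout come from week 11, and all 24 baseline records carry burnout. The information that visit alone holds about the label is H(r/48) − ½·H(r/24), where H is the entropy of a two-class label with that proportion:
  - r = 4: 0.414 − ½(0.650) = 0.089 bits
  - r = 8: 0.650 − ½(0.918) = 0.191 bits
  - r = 12: 0.811 − ½(1.000) = 0.311 bits

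A feature that recorded nothing except which visit it came from would therefore have positive mutual information with the pooled burnout label.

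**The case against.** The strongest reply is that the protocol never names burnout yes/no at baseline as the label for the QMI step. The algorithm text is generic, and its control-versus-patient contrast is only an example. Burnout against no burnout is a planned binary outcome, remission is tracked, and treatment response has its own endpoint. Participants can also differ at baseline in which second subscale qualified them, so subtype labels could exist. Choosing a label and visit is ordinary SAP detail, and the SAP is not shown.

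Much of this stands. A reader might infer that no second class exists anywhere and that the rule keeps nothing in the whole Storyline analysis. The documents do not support that, because the later assessments and the response endpoint supply classes. A reader might also infer that any follow-up contrast is fully confounded with visit, repeat exposure and treatment. That is not supported either: within one visit, remitters and non-remitters share visit and exposure, and either arm can supply either class. Strong confounding arises only if visits are pooled, which the protocol does not say it will do.

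What does not stand is the appeal to the SAP. An SAP can choose a label, but it cannot supply the group without burnout that eligibility excludes. A baseline subtype label separates kinds of burnout and does not diagnose burnout.

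One further caveat is fair. The MBI is taken at screening, up to 35 days before the first session, and again at week 1, while Table 2 lists the eligibility check only at screening. A score could drift below the threshold by week 1, although Section 5 requires continued eligibility.

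**Conclusion.** The point holds for the baseline recordings. They cannot support a marker that diagnoses burnout, and with burnout yes/no as the label exactly 0 features pass QMI > 0. That result is algebraic and does not depend on tuning. It assumes that continued eligibility is upheld, so that everyone still meets the definition at week 1.

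It does not extend to the later visits or to the response endpoint, where classes can exist. Analyses there may be informative about remission or response, but they do not answer the diagnostic question. The simulated counts and the pooled-visit figures rest on assumed settings and remission numbers, and they show direction and rough size only.

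Severity is low. The analysis is exploratory, and the safety, feasibility and QIDS-SR-16 conclusions do not depend on it.

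**What to change.** - In Sections 1.3 and 12.2, define the burnout endpoint as the association of baseline Storyline features with the continuous MBI emotional exhaustion score. State that entry restricts this score to 27 or above, which narrows its range.
- Keep class-based selection for baseline features that predict response or remission at week 11.
- State that visits will not be pooled to create a burnout label.
- Remove the words diagnosing (Section 2) and diagnostic (opening of the Exploratory Analysis, Section 12.2).

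The cost is wording in three sections, with the same participants and the same data. The downside is a narrower claim. A range-restricted score set against more than 20,000 features in 24 people can only generate hypotheses, and the text should say so.

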We will also assess the correlation between magnitude of change in burnout scores on the MBI using Pearson correlation. Path analysis will be used to assess changes in the Mystical Experience Questionnaire (MEQ-30), Challenging Experience Questionnaire, and Nondual Awareness Dimensional Assessment (NADA) as mediators of the effect of treatment (MBSR+PAP vs MBSR alone) on burnout, using bootstrapping to assess the significance of the indirect effect (Preacher & Hayes, 2008).

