##### Mystical Experience Questionnaire (MEQ30)

Looking back on the entirety of your psychedelic session, please rate the degree to which at any time during the session you experienced the following phenomena. Answer each question according to your feelings, thoughts, and experiences at the time of the psychedelic session. In making each of your ratings use the following scale:

0 – none; not at all

1 – so slight cannot decide

2 – slight

3 – moderate

4 – strong (equivalent in degree to any other strong experience)

5 – extreme (more than any other time in my life and stronger than 4)

|  | 0 | 1 | 2 | 3 | 4 | 5 |
| --- | --- | --- | --- | --- | --- | --- |
| Loss of your usual sense of time. |  |  |  |  |  |  |
| Experience of amazement. |  |  |  |  |  |  |
| Sense that the experience cannot be described adequately in words. |  |  |  |  |  |  |
| Gain of insightful knowledge experienced at an intuitive level. |  |  |  |  |  |  |
| Feeling that you experienced eternity or infinity. |  |  |  |  |  |  |
| Experience of oneness or unity with objects and/or persons perceived in your surroundings. |  |  |  |  |  |  |
| Loss of your usual sense of space. |  |  |  |  |  |  |
| Feelings of tenderness and gentleness. |  |  |  |  |  |  |
| Certainty of encounter with ultimate reality (in the sense of being able to “know” and “see” what is really real at some point during your experience. |  |  |  |  |  |  |
| Feeling that you could not do justice to your experience by describing it in words. |  |  |  |  |  |  |
| Loss of usual awareness of where you were. |  |  |  |  |  |  |
| Feelings of peace and tranquility. |  |  |  |  |  |  |
| Sense of being “outside of” time, beyond past and future. |  |  |  |  |  |  |
| Freedom from the limitations of your personal self and feeling a unity or bond with what was felt to be greater than your personal self. |  |  |  |  |  |  |
| Sense of being at a spiritual height. |  |  |  |  |  |  |
| Experience of pure being and pure awareness (beyond the world of sense impressions). |  |  |  |  |  |  |
| Experience of ecstasy. |  |  |  |  |  |  |
| Experience of the insight that “all is One”. |  |  |  |  |  |  |
| Being in a realm with no space boundaries |  |  |  |  |  |  |
| Experience of oneness in relation to an “inner world” within. |  |  |  |  |  |  |
| Sense of reverence. |  |  |  |  |  |  |

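### The Storyline analysis selects features on the outcome classes before cross-validating, which inflates accuracy even in pure noise; separately, MEQ-30 has no valid comparator value as a mediator

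*Protocol*

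**What the plan says.** The Storyline algorithm (Protocol 12.2, Exploratory Analysis) has three steps.

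1. *Rapid Question Filtering* computes "the variance for each measured feature for each question in the data for all people" and prunes the low-variance questions. It does not use outcome labels.
2. *Feature Selection* starts from a very large pool: "Storyline AI measures over 20,000 speech, vocal and facial features from the responses for each question". Random-forest importance is converted to a 'Preference' score and multiplied by mutual information to give QMI, and features with QMI above zero are kept. The criterion depends on the outcome: "The usefulness of the features is determined from their ability to differentiate the two classes in a study".
3. *Question Selection* fits a two-layer neural network to the kept features: "the input is all of the candidate questions and their optimized speech, vocal and facial features revealed from Short Story Score #2". Cross-validation appears only here: "questions are tested in all possible pairwise combinations with 5-fold cross validation". Each pair is given an index. A question's score sums index times mean accuracy over its pairs and is then rescaled to 0-100. The ranking and the mean accuracies are the stated final results.

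Section 4.2 gives the size: "This study will enroll a total of 24 patients with 12 patients in each study arm".

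The path analysis (12.2, Statistical Analyses, and again at the end of the Exploratory Analysis) takes changes in MEQ-30, the Challenging Experience Questionnaire and NADA "as mediators of the effect of treatment (MBSR+PAP vs MBSR alone) on burnout". The second statement specifies state and trait NADA and adds the Brief Savoring Inventory. The MEQ-30 form opens: "Looking back on the entirety of your psychedelic session".

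**The concern.** Cross-validation estimates performance on unseen people only if those people played no part in building the model. If features are chosen with everyone's outcome label and the folds are formed afterwards, each held-out person has already influenced the choice. With some 20,000 candidates per question and 24 people, many features separate the classes by luck, and the held-out people share that luck.

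Section 1.3 makes phenotypic predictors of burnout and of treatment response tertiary endpoints meant to inform later research, and the Background says the study will build a model to diagnose burnout and predict response. An accuracy figure that looks good with or without signal would mislead that research.

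The mediation question is separate. A mediator of a comparison between arms needs a meaningful value in both arms, and a change score needs at least two measurements.

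**Working it through.** The protocol states no accuracy, power or sample size for the Storyline analysis, so there is no figure to reproduce. The described sequence was simulated on data with no signal.

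**Inputs from the Protocol:** 24 participants (4.2); 20,000 features per question, in three blocks (speech, vocal, facial) run separately; random-forest importance times mutual information, keeping values above zero; a network on pairs of questions; 5-fold cross-validation.

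**Assumptions, because the Protocol does not give them:** independent normal features; one pair of questions; 100 or 500 trees; one hidden layer of 16 units; stratified folds; raw importance in place of the undefined 'Preference' score. The outcome split is also not given (12 and 12 is the split by arm), so 12/12 and 8/16 were both tried.

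**Selection on all 24, then cross-validation, pure noise:**

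| Classes | Rule | Runs | Features kept per question | Accuracy |
|---|---|---|---|---|
| 12/12 | QMI > 0, 100 trees | 12 | about 428 | 100% in every run |
| 12/12 | QMI > 0, 500 trees | 4 | about 1,780 | 100% in every run |
| 12/12 | top 20 only, 100 trees | 12 | 20 | 100% in every run |
| 8/16 | QMI > 0, 100 trees | 12 | about 394 | 100% in every run |
| 8/16 | QMI > 0, 500 trees | 4 | about 1,626 | 100% in every run |
| 8/16 | top 20 only, 100 trees | 12 | 20 | mean 99%, minimum 96% |

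**Selection repeated inside each training fold (QMI > 0, 100 trees, 12 runs each):** 48% (SD 8 points) with 12/12 classes, where chance is 50%; 58% (SD 10 points) with 8/16, where always guessing the larger class gives 16/24 = 67%.

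**Weakest reading.** If the 'Preference' conversion leaves every feature positive, only mutual information above zero selects, and about 45% of features survive. Four reduced runs (one question, 6,000 features, 8 hidden units, 12/12) gave 63%, 55%, 100% and 62%: mean 2.80/4 = 70%. With no selection, the same data gave 47%.

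**Index multiplier.** The Protocol does not define the index. Suppose it is a serial number, with 10 questions, 45 pairs numbered in list order, and the same accuracy A for every pair.
- Question 1 is in pairs 1 to 9: sum = 45A.
- Question 10 is in pairs 9, 17, 24, 30, 35, 39, 42, 44 and 45: sum = 285A.

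These are the smallest and largest sums, so after rescaling the two questions score 0 and 100 although they predict equally well.

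**Mediators against Table 2 and the printed forms:**

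| Measure | Scheduled | Fits the MBSR arm? |
|---|---|---|
| MEQ-30 | week 7 only | No: asks about a psychedelic session |
| Challenging Experience Questionnaire | week 7 only | Unclear: printed form names no psychedelic session |
| NADA, state | weeks 7 and 8 | Unclear: asks about what was just experienced |
| NADA, trait | weeks 1 and 11 | Yes |
| Brief Savoring Inventory | weeks 1 and 11 | Yes |

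MEQ-30 and the Challenging Experience Questionnaire therefore have no change score. If MEQ-30 were set to zero in the MBSR arm, the paths would be M = a·T and Y = c0 + c′·T + b·M. Then a is the mean MEQ-30 in the MBSR+PAP arm. Because M does not vary in the MBSR arm, b is exactly the slope within the MBSR+PAP arm (12 people planned). The product a·b can be calculated, but it only extrapolates that slope down to zero.

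**The case against.** **Fold structure can be left to a SAP, and use of all participants is explicit only for the variance filter.** Both statements are correct. For step 2 the use of everyone is inferred. But the Protocol does fix the order: selection on the classes, then cross-validation of the features already chosen, with the resulting accuracy as a final output. Followed as written, it is biased.

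**A reader might infer that accuracy will be close to 100% whatever the data.** The document does not support that. The figure depends on the undefined 'Preference' conversion and falls to about 70% on the weakest reading. The Protocol also says that many features are correlated, whereas the simulation used independent ones. The direction of the bias stands; its size is a range.

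**A reader might infer that all the mediators exist only in the MBSR+PAP arm.** They do not. Trait NADA and the Brief Savoring Inventory fit both arms. A footnote to Table 2 says questionnaires are assessed similarly in both arms, and week 7 is also the MBSR retreat, so the Challenging Experience Questionnaire and state NADA could be completed there. Only MEQ-30 is excluded by its own wording.

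**A reader might infer that an indirect effect through MEQ-30 cannot be estimated.** With zeros in the MBSR arm it can be computed. The difficulty is what it means.

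**That the index makes ranking depend on list order** holds only if the index is a serial number. What stands without that assumption is that it is undefined.

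**All of this is exploratory.** Agreed, and that limits its weight.

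**Conclusion.** The order of steps in the Storyline analysis is wrong as written. With 24 participants and pure noise, reported accuracy would be about 99-100% if unused features score zero, or about 70% (range 55-100% over four reduced runs) if every feature's 'Preference' score is positive. Selection repeated inside the folds, checked under the first of these readings, performs no better than chance. The sizes rest on independent features, the network and forest settings listed above, and step 2 using all participants.

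The mediation statement needs narrower correction. MEQ-30 has no valid MBSR value, and neither MEQ-30 nor the Challenging Experience Questionnaire has a change score. Use of the Challenging Experience Questionnaire and state NADA in the MBSR arm needs to be stated.

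Safety, feasibility and the primary QIDS-SR-16 comparison are unaffected.

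**What to change.** - State that step 2 and any choice of question pair are carried out inside each training fold. The variance filter may stay outside, since it does not use the labels.
- Report only the outer-fold accuracy, with a p-value from permuting the labels and rerunning the whole sequence.
- Define the 'Preference' conversion.
- Replace the index-weighted sum by the mean accuracy over the pairs that contain the question.
- Analyse MEQ-30 as an association within the MBSR+PAP arm, as section 1.3 already plans.
- Keep trait NADA and the Brief Savoring Inventory in the path model. Include the Challenging Experience Questionnaire and state NADA only if they are actually given in both arms, and use them as post-session scores where there is no baseline.

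The cost is revised analysis wording and more computing time. The downside is that reported accuracies will be less favourable. No additional participants or visits are needed.
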